### Validity and reliability

Reliability will be ensured by using consistent standardised verbal instructions. Reliability will be improved by doing the data collection in a standardised environment and by implementing standardised procedures. Validity of the patients’ responses will be confirmed by member checking.

### Ethical considerations

Ethical clearance will be obtained from the University of the Witwatersrand Human Research Ethics (Medical) Committee. Permission will be obtained from the management of Chris Hani Baragwanath Academic Hospital (CHBAH) and the head of the physiotherapy department where the study is to be conducted. Once ethical clearance is obtained, the study will commence and continue for a period of a year to ensure a sufficient sample for statistical analysis.

Participants will not receive any remuneration for participating in this study. This study is completely voluntary, and the patient may choose to withdraw at any point, without giving a reason and at no risk or penalty. Confidentiality will be maintained by keeping the participants’ names anonymous and by using identifiers on the outcome measures and data-recording sheets. In the event of identifying patient or caregiver ‘distress’ during telerehabilitation sessions, immediate referral will be made to the CHBAH’s Psychiatry Department, and this will be recorded in the patient’s file. Procedure for referral is outlined in the Distress Protocol (Appendix 7). All ethical guidelines will be adhered to as stipulated by HPCSA regulations regarding the provision of telerehabilitation.

The ethical approval was received from the Human Research Ethics Committee (Medical) University of the Witwatersrand M200772. The ethical approval was provided with the condition that ethics training certificates of all researchers are provided.

### Ethical considerations specifically relating to the paediatric participants

The patient’s caregiver is at liberty to ask questions and seek clarification of the procedures and telerehabilitation in general. The patient’s primary caregiver may at any time ask that the telerehabilitation consultation process be stopped, without future prejudice. An alternative way of safe and ethical follow-up would be considered so that treatment is continued as possible. If the proposed route of telerehabilitation delivery cannot be done because of device or connectivity limitations, the child should still be followed up in other appropriate and safe ways. No videos or images of the child should be sent to therapists on social media platforms.

A ‘form 22’ will be completed in the case of any suspected ‘abuse’, and appropriate and immediate referrals will be made to social services. A copy of this form will be attached to the telerehabilitation recording template. The consulting practitioner’s name as well as the scribe’s name (if applicable) and contact details and location will be recorded. There will be adherence to child protection principles (in the *Children’s Act* 38 of 2005) at all times. The HPCSA guidelines for Privacy and Confidentiality and Protection of Personal Information will be adhered to at all times.

Continuity of care should be facilitated, and practitioners are to ensure that telerehabilitation services meet the same standards of professional, legal, quality and ethical standards as services provided in person. The patient’s caregiver should acknowledge the risks of telerehabilitation consultation in respect of the technology used or assessment made by the practitioner or any physical injury sustained by the child whilst carrying out the HEP. Every effort will be made by the practitioner to mitigate these.

## Discussion

The COVID-19 pandemic demanded a vast change in the dynamics of healthcare delivery. Despite telerehabilitation growing as a mode of healthcare delivery in recent years, its uses in public health settings have been limited because of the lack of awareness and reservations (Odole et al. 2015). Our study will therefore enable us to explore the implementation and application of telerehabilitation in a public health setting to provide continuity of care in the COVID-19 pandemic as well as its long-term application. Eriksson, Lindström and Ekenberg (2011) highlights that the relationship formed between therapist and patient is vital during rehabilitation and stresses that this should not be compromised during telerehabilitation. Our study is therefore designed to ensure that patient engagement is maximised during the session as patient satisfaction with services is crucial to ensure improved compliance. Furthermore, the procedure of our study has been adjusted to accommodate for limited resources in our setting as in our context therapists do not have access to bulk SMS system, appointment systems, ‘apps’, bulk email system, encryption software, readily available databases for exercises or additional funding for this. Most of our patients do not own smart phones, have limited or no access to Wi-Fi or do not have data or the money for data. Hence, the procedure was designed primarily to have telephonic conversation with the patients where the therapist calls the patient to send and receive WhatsApp messages or in the rare circumstances to send and receive emails. Funding will be applied for from various institutions for the purchase of necessary equipment such as Wi-Fi routers and external hard drives as well as data and/or airtime for participants and researchers.

Outcomes of the study will allow us to explore the effectiveness of telerehabilitation improving access to care, quality of care, short- and long-term outcomes, patient and therapist satisfactions and the use of human resources. Results from our study will therefore explore both clinical outcomes as well as perceptions of telerehabilitation to gain an in-depth understanding of its efficacy, thereby determining its role in a public health setting.

Findings will be disseminated by means of publications in relevant accredited journals like the South African Health System Review to advise policymakers on the efficacy of such systems. It will be presented at various conferences and symposiums and, in addition, will be presented in several forums like Physiotherapy Forum, Rehabilitation Forum, CHBAH Research Day, Ekurhuleni Research Day and other symposiums to disseminate the information in the context it was studied on.

### Limitations

The participants’ understanding and insight into their condition and their performance will impact the accuracy of the responses. The therapist will also have to accurately rely on the patients presenting themselves as well.

## Appendix 3

### Resource survey of devices and data for tele-health paediatrics: English

**Table d31e1150:**

**Patient name:**	
**Diagnosis:**	
**Age:**	**Consent:**
**Contact no 1:**	
**Contact no 2:**	
Would you be interested in doing tele-rehab?	
In what area do you live?	
Do you have a landline at home?	
Do you have access to a cell phone or any smartphone?	yes – my own yes – someone in my family no – don’t have a cell phone
Do you have internet access at home?	yes no
Do you have an email address?	Yes – my own Yes – someone in my family No
Is there someone at home who can help you with completing a telerehabilitation programme and the setup of your phone?	

## Appendix 4

### Subjective assessment framework questions paediatrics: English

**Table d31e1220:**

CATEGORY	ITEM	QUESTION TO BE ASKED
**Patient progress** and **general concerns** regarding the child	Progress/changes since last therapy visit	HOW HAS YOUR CHILD CHANGED SINCE YOUR LAST VISIT? ANYTHING NEW HE/SHE HAS LEARNT TO DO?
	General concerns about the child	WHAT ARE YOU WORRIED ABOUT CONCERNING YOUR CHILD?
**Physical activities/functional abilities/highest functional level**	Caregiver concerns	ARE YOU WORRIED ABOUT ANYTHING WITH YOUR CHILD’S **BODY**? ARE YOU WORRIED ABOUT WHAT HIS BODY CAN DO?
	Physical/gross motor abilities	WHAT CAN YOUR CHILD **DO** WITH HIS BODY? eg rolling, sitting, crawling, standing, walking, using hands for play and feeding.
	Current HEP	WHAT **EXERCISES** ARE YOU DOING WITH YOUR CHILD?
	Frequency of HEP	HOW **OFTEN** ARE YOU DOING THE EXERCISES?
	Available equipment at home	WHAT **TOYS or EQUIPMENT** ARE YOU USING TO HELP YOU DO THIS?
	Who carries out the HEP	**WHO** DOES THE EXERCISES WITH YOUR CHILD?
	Difficulties with the HEP	WHAT IS **DIFFICULT** OR NOT WORKING WELL WITH THE EXERCISES?
	Compliance with referral/s	DID YOU ATTEND……… (relevant clinic or service)?
		(NB: check status of **hips** and need for **X-ray or Orthopedic** follow up)
**Specific Physical difficulties**: gait, balance, muscle strength, joint stiffness (FOR ORTHOPAEDIC CASES)	Concerns about the strength of body or certain joint/s	DO YOU SEE A **WEAKNESS** IN ANY PART OF YOUR CHILD’S BODY?
	Concerns about the ROM of certain joint/s	ARE THERE PARTS OF THE BODY THAT DON’T **MOVE AS WELL** AS THEY SHOULD? (Ask about the specific joint/s and the amount of movement in each direction).
	Concerns about walking/gait	ARE THERE PROBLEMS WITH YOUR CHILD’S **WALKING**? PLEASE EXPLAIN…. IS HE USING ANYTHING TO HELP HIM WALK?
	Concerns about balance	DOES YOUR CHILD HAVE POOR **BALANCE** or IS CLUMSY?
	Current HEP	WHAT **EXERCISES** ARE YOU DOING WITH YOUR CHILD?
	Frequency of HEP	HOW **OFTEN** ARE YOU DOING THE EXERCISES?
	Who carries out the HEP	**WHO** DOES THE EXERCISES WITH YOUR CHILD?
	Difficulties with the HEP	WHAT US **DIFFICULT** OR NOT WORKING WELL WITH THE EXERCISES?
	Compliance with referral/s	DID YOU ATTEND……… (relevant clinic or service)?
**Communication/auditory/visual abilities**	Caregiver concerns	ARE YOU WORRIED ABOUT ANYTHING WITH YOUR CHILD’S **TALKING, RESPONDING, SEEING or HEARING?**
	Current HEP	WHAT **ACTIVITIES** ARE YOU DOING TO HELP THESE?
	Available toys/equipment at home	WHAT **TOYS or EQUIPMENT** ARE YOU USING TO HELP YOU DO THIS?
	Compliance with referral/s	DID YOU ATTEND……… (relevant clinic or service)?
		(NB: check status of **hearing** and need for **Audiology** follow up)
		(NB: check status of **vision** and need for **St John’s** follow up)
**Feeding and growth**	Caregiver concerns	ARE YOU WORRIED ABOUT ANYTHING WITH YOUR CHILD’S **EATING AND DRINKING?**
	Growth curve in the Road To Health Card (RTHC)	HOW IS YOUR CHILD **GROWING** IF YOU LOOK AT THE RTHC? (help the mom to look at the curve or ask for a photo of the growth curve)
	Specific difficulties	IS THERE OFTEN **COUGHING OR VOMITING** WITH FEEDING? (Ask about amount and frequency). HOW LONG DOES IT TAKE TO FEED YOUR CHILD? (ask about solids and liquids)
	Current HEP	WHAT **ACTIVITIES** ARE YOU DOING TO HELP YOUR CHILD?
	Compliance with referral/s	DID YOU ATTEND……… (relevant clinic or service)?
**Use of orthotics, walking aids, seating devices, standing devices**	Nature of devices/orthotics	WHAT **ITEMS (splints)** or **EQUIPMENT** IS YOU CHILD USING: eg to sit, stand, keep his feet and legs straight? Any SPLINTS for HANDS?
		(**NB**: think about buggy/wheelchair, standing device, AFO’s, key-stones, hand splints: soft or hard)
	Frequency of usage	How **OFTEN** are you using these? In the **DAY** or at **NIGHT?**
	Difficulties encountered	Are they **FITTING** WELL? Do you have any **PROBLEMS** using these? Are they **BROKEN** or TOO **SMALL**?
	Compliance with referral/s	DID YOU ATTEND……… (relevant clinic or service)?
**General COPING**	Caregiver feedback	ARE YOU **COPING** WITH YOUR CHILD? ANY CONCERNS or OTHER PROBLEMS?
**GAS GOALS SET**	Set modified GAS GOAL that is measurable without having to see the child or send images of the child.	1) What do you want your child to be able to do in 3 months’ time? 2) Something that will be possible for him/her? 3) Think about the body, play and communication. (then wait for caregiver’s response) 4) How about this? (give one or two ideas for caregiver to think about) 5) Would you like to set this as a goal for us to work towards? 6) Then in 3 months we will see how far he/she has come and how to help him/her further. ***(NB: allow the caregiver time to think about this and confirm with you at the next call if he/she is unsure)***
**GAS GOALS MET**	Evaluate at 3 months	7) Do you remember the goal we set for your child? 8) Do you think he/she has achieved this? 9) What makes you say this? ***(NB: help the caregiver to see what part/s of the goal the child has achieved/partially achieved)***

## Appendix 5

### Caregiver questionnaire English

Please answer questions 1 to 10 and give a brief comment and suggestion for all questions.

**Table d31e1575:**

1.	Did you enjoy the experience of tele-rehab for you and your child?	Yes	No	N/A	Comments and/or Suggestions		
2.	Do you feel like you learnt better how to help your child during tele-rehab?	Yes	No	N/A	Comments and/or Suggestions		
3.	What was difficult for you during the tele-rehab calls and treatment?	Yes	No	N/A	Comments and/or Suggestions		
4.	Was your culture and language respected during the calls and treatment?	Yes	No	N/A	Comments and/or Suggestions		
5.	Was the therapist’s attitude friendly and caring towards you?	Yes	No	N/A	Comments and/or Suggestions		
6.	Were you able to use any of the videos or pictures that were sent to you?	Yes	No	N/A	Comments and/or Suggestions		
7.	Were you given the chance to ask questions about your child’s treatment?	Yes	No	N/A	Comments and/or Suggestions		
8.	Where you given the right to refuse tele-rehab treatment?	Yes	No	N/A	Comments and/or Suggestions		
9.	Do you feel your child has benefitted from the advice and exercises given during tele-rehab?	Yes	No	N/A	Comments and/or Suggestions		
10.	How likely are you to recommend tele-rehab to another parent?	Very low	Low	Not sure	High	Very high	Comment and/or suggestions:

## Appendix 6

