Frequencies and proportions will be used to summarise categorical variables. The two samples proportions test will be used to compare if there are any differences between the Yes or No responses. Comparisons between proportions with categorical variables will be performed by using the Chi squared test with the condition that the assumption is met:

5.Qualitative information will be gathered from two sources. The therapist’s experiences will be collected as positive, negative, challenges and other, and if further subthemes emerge from those categories, it will be described verbatim. In the subjective framework of questions, patients are asked a directed open-ended question on their experience of the call and the telerehabilitation sessions. The responses will also be categorised into themes that emerge.

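### Caregiver questionnaire item 3 asks an open question but offers Yes/No/N/A boxes, so its planned Yes/No proportion has no defined meaning

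*Protocol article*

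**What the plan says.** Appendix 5 of the Protocol article prints the ten-item questionnaire that gathers paediatric caregivers' perceptions at the final consultation. Its instruction is "Please answer questions 1 to 10 and give a brief comment and suggestion for all questions". Items 1 to 9 all carry the same response cells: Yes, No, N/A and a field for comments or suggestions. Item 1, for example, is "Did you enjoy the experience of tele-rehab for you and your child". Item 3 is "What was difficult for you during the tele-rehab calls and treatment". Item 10, "How likely are you to recommend tele-rehab to another parent", has its own five-point scale from very low to very high.

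For the experience objective (number 4 in the Statistical analysis section), the plan states "Frequencies and proportions will be used to summarise categorical variables" and then "The two samples proportions test will be used to compare if there are any differences between the Yes or No responses". No item is excepted. On free text, the same section says "Qualitative information will be gathered from two sources". It names them as the therapists' experiences and an open-ended question in the subjective framework. The comments on the Appendix 5 form are not named.

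**The concern.** An open question has been put into a row built for closed ones. The caregiver is told to answer every item, so many will tick a box in item 3, but the form does not say what a tick means. The analysis section then treats Yes/No ticks as categorical data to be summarised and tested.

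What is at stake is the information on what caregivers found hard about the calls and treatment. The Discussion says that most patients have no smartphone and have little or no Wi-Fi or data, so difficulty with remote delivery is a natural thing to want to know here. Item 3 is the only item on this form that asks about it directly. As the plan reads, the part of item 3 with an assigned analysis (the tick) cannot be interpreted, and the part that can be interpreted (the comment) has no assigned analysis. An ambiguous tick cannot be given a meaning after it has been collected.

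**Working it through.** The plan gives no figure for this point and none is needed. The check is a reading of the form against the analysis text.

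**1. Count of items by format.** Ten items in total. Item 10 is on a five-point scale, which leaves 10 − 1 = 9 with Yes/No/N/A cells. Item 3 is the only one of these that is an open question, which leaves 9 − 1 = 8 closed items (1, 2 and 4 to 9).

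**2. Direction of Yes.** In each of those 8 closed items Yes is the favourable answer: enjoyed it, learnt better, culture and language respected, therapist friendly, materials usable, able to ask questions, able to refuse, child benefited. On item 10 a high rating is favourable.

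**3. What a tick on item 3 could mean.**
- Yes: something was difficult, or a habitual tick down the Yes column.
- No: nothing was difficult, or nothing to report.
- N/A: nothing was difficult, or the boxes do not fit and the answer is in the comment.

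A caregiver who had difficulty could end up under Yes or N/A. One who had none could end up under any of the three. The share ticking Yes therefore neither estimates nor bounds the share who had difficulty. The claim that item 3 runs against the other items holds only if Yes is read as 'there was a difficulty', and the form does not fix that reading.

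**4. Form against analysis.** The proportions and the two-sample test are stated for Yes/No responses generally, so item 3 is included as written. The qualitative paragraph names two sources, and the Appendix 5 comments are neither of them.

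**5. Is the same information collected elsewhere?** Appendix 4 has an entry headed "Difficulties with the HEP". It concerns the home exercise programme, not the calls. Appendix 4 also asks about problems with devices and about coping in general. None of these asks directly what was difficult about the telerehabilitation calls.

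**6. Is it a fault of text extraction?** Nothing suggests so. The item 3 row is complete and matches its neighbours, and the different scale of item 10 came through intact.

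**The case against.** The strongest reply is that the content is not lost. The form asks for a comment on every question, item 3 has a comments field, and most caregivers will naturally answer a 'what' question there. This stands in part: the text may well be usable. But the article names its qualitative sources and these comments are not among them. A full protocol or analysis plan may assign them, but it could not repair the tick.

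A second reply is that the pilot, which is meant in part to find errors in the methodology, could expose the misfit. It could, but nothing ensures that it will.

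A third is that caregivers' problems are sought at every follow-up through Appendix 4. That is true of problems with exercises, devices and coping, so 'only item on difficulties' must be limited to the questionnaire.

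Two stronger readings are tempting, and the documents support neither. A reader might infer that item 3 distorts an overall satisfaction rate, because difficulty would be counted as a good answer. The plan describes no pooled Yes rate or summed score. If items are reported one by one, item 3 cannot change any other item's result, and each line carries its own question. A reader might also infer that the questionnaire has no valid measure of negative experience. It has several: No on items 1, 2 and 4 to 9, and a low rating on item 10.

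**Conclusion.** The defect is real and small. Item 3's response boxes do not fit its wording. The plan includes its Yes/No ticks in proportions and a test without exception, and the result would have no defined meaning. It affects one of nine Yes/No items, on one form, for paediatric caregivers, within the experience objective. The other nine questionnaire items and the clinical-effect objectives are untouched.

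The conclusion rests on the form being used as printed and on the analysis section applying to all its Yes/No items. It needs no assumed response rate. The unfavourable direction of Yes is conditional on how caregivers read the item; that the tick is uninterpretable is not. This is a minor correction, worth making because it is nearly free before use and cannot be recovered afterwards.

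**What to change.** Before the form is used, reword item 3 as a closed question with a follow-up, for example: *Was anything about the calls or the treatment difficult for you? Yes / No. If yes, what?* Make the same change in every language version. In the analysis text, state that Yes on item 3 is unfavourable and that the item is reported on its own line, and add its free text to the thematic analysis as a named source.

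If forms have already been completed, treat item 3 as free text only and exclude its ticks from the Yes/No proportions and tests.

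The cost is one line on each language version of the form, one line of coding, and one sentence in the analysis section. There is no effect on sample, schedule or the other items.

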Consistency and reliability during the proposed telehealth sessions will be ensured by following the telehealth guidelines set out by the SASP during 2020 and the HPCSA in 2014 and 2020. Participants will be asked to provide feedback for the orthopaedics and NMS subgroup and to complete a questionnaire for the paediatric population to provide their perceptions and experiences of telerehabilitation. For all interactions, attempts will be made to communicate with participants in their language of choice.

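### Caregiver items 4 and, less strongly, 9 each put two attributes under one Yes/No tick, so a No cannot be attributed and a mixed experience has no accurate answer

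*Protocol article*

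**What the plan says.** Appendix 5 of the protocol article has ten items. Items 1 to 9 offer Yes, No or N/A with a comment column; item 10 uses a five-point scale.

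- Item 4: "Was your culture and language respected during the calls and treatment"
- Item 9: "Do you feel your child has benefitted from the advice and exercises given during tele-rehab"
- The instruction at the head of the form: "Please answer questions 1 to 10 and give a brief comment and suggestion for all questions"

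Caregiver experience is a stated objective. Under the experiences objective, the Statistical analysis section summarises categorical answers as frequencies and proportions, then adds: "The two samples proportions test will be used to compare if there are any differences between the Yes or No responses". The paragraph on qualitative information names two sources: therapists' experiences, and an open-ended question in the subjective framework. The Appendix 5 comment column is not named as either.

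On language, Methods and design offers English or Zulu, and says of all interactions that "attempts will be made to communicate with participants in their language of choice".

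**The concern.** The datum that is counted and tested is the tick. On items 4 and 9 the tick covers two attributes that could differ in this study.

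- **Item 4.** Language provision is partly a matter of best effort, while cultural respect depends on the therapist's conduct. A caregiver treated courteously but not in her own language has no box that fits. This is the only Appendix 5 item about language.
- **Item 9.** Advice can be given by voice on any telephone. The paediatric exercise database consists of videos and images, which need a device and data. This is the only Appendix 5 item that asks about benefit to the child.

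At stake is whether the study can say which component of the service needs changing. If item 4 attracts many No answers, the ticks will not show whether to improve language cover or cultural conduct. That information cannot be recovered from the ticks afterwards.

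**Working it through.** The plan states no sample size, expected response rate or target for these items, so there is no figure to reproduce. The check has two parts.

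**1. Literal reading: Yes means both parts held.** Let *q* be the share ticking No, with *a* and *b* the shares for whom the first and second part failed. A No is ticked when at least one part fails, so

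max(*a*, *b*) ≤ *q* ≤ *a* + *b*.

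An observed *q* therefore fits *a* = *q* with *b* = 0, and equally *a* = 0 with *b* = *q*. A Yes is clear on this reading; a No is not attributable. This needs no assumed rates.

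**2. How far the reading itself could matter (illustration only).** Let pA and pB be the shares for whom each part held. The bounds on the Yes share are

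- both required: from max(0, pA + pB − 1) to min(pA, pB);
- either enough: from max(pA, pB) to min(1, pA + pB).

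The rates below are assumptions; the documents give none.

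| Item | pA | pB | Both required | Either enough | Smallest gap |
|---|---|---|---|---|---|
| 4 (culture, language) | 0.95 | 0.70 | 0.95 + 0.70 − 1 = 0.65, to 0.70 | 0.95 to 1.00 | 0.95 − 0.70 = 0.25 |
| 9 (advice, exercises) | 0.80 | 0.50 | 0.80 + 0.50 − 1 = 0.30, to 0.50 | 0.80 to 1.00 | 0.80 − 0.50 = 0.30 |
| 4, parts equal | 0.95 | 0.95 | 0.95 + 0.95 − 1 = 0.90, to 0.95 | 0.95 to 1.00 | 0.00 |

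The smallest gap between readings equals the difference between pA and pB. It can vanish when the two parts succeed equally often, as in the last row. The gap also needs some caregivers to read *and* as *or*. On the literal reading, item 4 in the first row stays within 65–70%.

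**Can the rest of the form separate the parts?** For item 9, partly: item 6 asks whether the videos or pictures sent could be used. That measures usability, not whether the exercises helped. For item 4, no other item touches language or culture. The comment column could separate the parts for both items, but no coding or reporting of those comments is stated.

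**The case against.** The strongest reply is that the form does not rest on a bare tick. Every row asks for a comment, and a caregiver with a mixed experience can explain it there. This stands in part. The comment can explain an individual answer, but the tested quantity is still the tick, and these comments are not among the two named qualitative sources.

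Further points against, and what remains of them:

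- **Item 9 as a package.** Advice and a home programme are delivered together, so the share benefiting from the package has a meaning. That is right, and it is why item 9 is the weaker case. The proportion still cannot separate the components.
- **Other evidence of benefit.** Appendix 4 asks about the child's progress and whether the three-month goal was met. Neither question identifies which component helped.
- **Device access.** The Discussion's remark that most patients lack smartphones describes patients generally. Paediatric families are screened by the resource survey in Appendix 3, and verbal guidance on the exercise programme is also possible. The remark therefore cannot be carried over to the caregivers who complete this form.
- **Language cover.** The arthroplasty procedures put a fluent therapist in the lead where the preference is not English, with a family member as the alternative. Language failure may therefore be uncommon, but item 4 could not show whether it is.

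A reader might also count item 1, "Did you enjoy the experience of tele-rehab for you and your child", as a third case. It asks one respondent about a shared experience and is essentially a single question. Item 5, "Was the therapist’s attitude friendly and caring towards you", does join two words, but the attributes are close and little is lost.

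**Conclusion.** The point holds for item 4, and to a lesser degree for item 9. Each joins two attributes under one tick, a No cannot be attributed to either part, and the requested comments are only a partial remedy because their analysis is not stated.

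A reader might infer that the tested proportions have no fixed meaning, or that the reported figure could move by 25 points or more. The documents support neither. A literal Yes affirms both parts, so the ambiguity lies in No answers and in caregivers who answer for one part only. The 25-point gap rests on assumed rates and on an either-is-enough reading; it is an illustration, not an estimate. Nor is it shown that a Yes on item 9 would come from advice alone, which needs the same non-literal reading.

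This is a cheap improvement to a questionnaire. It exposes no contradiction and alters no stated figure.

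**What to change.** Make the change before data collection. The pilot announced in Methods and design, which is meant to find errors in the methodology, is the natural point.

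1. Replace item 4 with two items, one on respect for the caregiver's language and one on respect for her culture.
2. Replace item 9 with two items, one on the child's benefit from the advice and one on benefit from the exercises. Use the existing N/A box where no exercises were received.
3. Report each new item as its own proportion, and show the exercise-benefit item alongside item 6.

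The cost is two extra rows on the form and slightly longer completion. If the form cannot be changed, the fallback is to state how the comments on items 4 and 9 will be coded and to report the result beside the Yes/No split. That is weaker, because it depends on caregivers writing a comment that names the part that failed.
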